**Abstract**

**Objectives:** The aim of this study is to evaluate the quality of care (QOC) of the Hospital Authority’s (HA) patient empowerment programme (PEP) programme using an evidence-based structured and comprehensive evaluation framework to identify areas for quality enhancement.

**Design, Setting and Subjects:** A longitudinal study will be conducted using the Action Learning and Audit Spiral methodologies to measure whether the target standard of care intended by the PEP programme is achieved. Each PEP participating clinic and non-government organization (NGO) will be invited to complete a structured evaluation questionnaire. The data of all patients who have enrolled into the PEP for more than one year will be included in the evaluation on the process and outcomes of care. To determine a difference of programme performance and impact between group (PEP participants and non-participants), cohort study would be adopted. A cohort includes all eligible DM patients under care of HA GOPC at 1 Sep 2009 will be followed up on the clinical outcomes including HbA1c, blood pressure, lipids, and complications rates. To evaluate the effect of PEP on patient-reported outcomes, 550 participants, as well as 550 of those who have not participated in the PEP, will be recruited from each cluster and followed up by telephone to evaluate the effect of the programme on quality of life (QOL), patient enablement, global rating of change in health condition and private service utilization at baseline, 6, 12, 36 and 60 months after enrolment. Data on the process of care will be retrieved from the HA medical records. The cost effectiveness analysis (CEA) by mathematical modeling will be carried out by using cost and clinical outcome data provided by the HA, as well as quality-of-life and private service utilization cost data collected by the telephone surveys.

**Main Outcome Measures:** The primary outcomes are the proportion of participants who have received the planned process of care and achieved the target HbA1c and blood pressure levels.

**Data Analysis:** Descriptive statistics on proportions meeting the QOC criteria will be calculated. The changes in clinical, service, and patient reported outcomes at 6 and 12 months will assessed by paired sample t-test for each audit cycle. The audit cycle will be repeated annually over a period of 5 years.

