## Subjects

All patients who have been enrolled into the PEP programme will be included in the evaluation on process of care for each audit cycle; whereas all enrolled subjects who have been recruited for more than 12 months in the programme will be included in the evaluation on the clinical outcomes of care for each audit cycle.

To determine a difference of programme performance and impact between group (PEP participants and non-participants). A cohort of all eligible DM patients under care of HA GOPC at 1 Sep 2009 would be included for the monitoring of the changes in clinical and service utilization outcomes from Sep 2009 to Sept 2015.

550 patients who have enrolled into the PEP and 550 who have not taken part in the PEP will be invited in person from the general outpatient clinics by trained research assistants at the beginning of each evaluation cycle to take part in a telephone survey on patient reported outcomes for each cluster and written consent will be obtained (appendix A). All subjects who have given consent to the telephone follow-up survey will be interviewed by telephone within four weeks, at 6, 12, 36 and 60 months from recruitment to answer the SF-12 Health Survey on quality of life (QOL), the patient enablement Instrument, the Global Rating Scale (GRS) change in health, and a structured questionnaire on private service utilization rates.

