## Data Collection

Evaluation on structure and process

The co-ordinator of each participating clinic and all participating NGO will be asked to complete the structure of care questionnaire (appendix B). Anonymized data will be retrieved from the computerized medical record system (CMS) by the HA Statistics team to determine the patient recruitment rate, enrollment rate, attendance rate, compliance with assessment as per protocol, number of investigations and referral rate.

Evaluation on outcomes of care

Anonymized data on HbA1c, blood pressure (BP), low-density lipoprotein (LDL), body mass index (BMI) and annual attendance rates for GOPC, specialist outpatient clinic (SOPC) , accident and emergency (A&E) and hospital attendance rates, patient knowledge on disease at baseline and 12 months will be retrieved from the CMS by the HA Statistics team. The audit cycle will be repeated annually over a period of 5 years. This data will be extracted are shown in the data collection form in appendix C.

The 550 patients in the PEP programme who are willing to take part in the telephone survey will be contacted by a trained research assistant who will obtain verbal consent from each patient. Each patient will then answer the Chinese (Hong Kong) Short Form-12 version 2 (SF-12v2) Health Survey within one month from enrolment, and then at 6, 12, 36 and 60 months to repeat the SF-12v2 together with the Patient Enablement Instrument (PEI), Global Rating Scale (GRS) of change in health condition and private service utilization (appendix D).

- 1. The Chinese (Hong Kong) Short Form-12 version 2 (SF-12v2) Health Survey is a generic measure HR QOL. It has been validated and normed on the general Chinese population in Hong Kong (Lam, Wong et al. 2010). It measures eight domains on physical functioning, role physical, bodily pain, general health, vitality, social functioning, role emotional and mental health on a scale range from 0 to 100. A higher score indicates better HRQOL. The eight domain scores can be summarized into two summary scores, the physical (PCS) and mental (MCS) component summary.

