**病人自强量表**

參加了共同護理計劃後,您感到以下的情況有何改變?

(請於每行出最適合的答案)

|  | **大為改善** | **有所改善** | **一樣** | **少了** | **不適用** |
| --- | --- | --- | --- | --- | --- |
|  | **2** | **1** | **0** | **0** |  |
| a. 能夠應付生活 |  |  |  |  |  |
|  |  |  |  |  |  |
| b. 能夠了解自己的疾病 |  |  |  |  |  |
|  |  |  |  |  |  |
| c. 能夠面對自己的疾病 |  |  |  |  |  |
|  |  |  |  |  |  |
| d. 能夠保持自己身體健康 |  |  |  |  |  |
|  | **大為增强** | **有所增强** | **無甚改變** | **少了** | **不適用** |
| e. 對自己健康的信心 |  |  |  |  |  |
|  |  |  |  |  |  |
| f. 擁有自助的能力 |  |  |  |  |  |

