**整體健康轉變評估問卷**

參加了共同護理計劃後, 您認為您的身體健康情況比之前是 ……

(請出最適合的答案)

| 好了很多 | 好了 | 好了一點 | 一樣 | 差了一點 | 差了 | 差了很多 |
| --- | --- | --- | --- | --- | --- | --- |
| +3 | +2 | +1 | 0 | -1 | -2 | -3 |

多謝您參與研究！

-------------------------------------------------完-----------------------------------------------

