**The Patient Enablement Instrument**

As a result of your participation in Shared-Care Programme, do you feel you are….

(please  one box in each row):-

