**Global Rating on Change Scale**

How would you rate the change in your health condition after participating in the Shared Care Programme?

| **MUCH BETTER** | **BETTER** | **A LITTLE BETTER** | **SAME** | **A LITTLE WORSE** | **WORSE** | **MUCH**  **WORSE** |
| --- | --- | --- | --- | --- | --- | --- |
| +3 | +2 | +1 | 0 | -1 | -2 | -3 |

-------------------------------------------------end-----------------------------------------------

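### The PEI and GRS questions presuppose joining a Shared Care Programme, so non-participants cannot validly answer two secondary outcomes that the design text assigns to them

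*Protocol*

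**What the plan says.** **Who is to answer.** The Abstract states that "550 participants, as well as 550 of those who have not participated in the PEP, will be recruited from each cluster", and gives the purpose as evaluating the programme's effect on quality of life, enablement, global change and private service use. The Subjects section says "All subjects who have given consent to the telephone follow-up survey will be interviewed by telephone within four weeks" and then at the follow-up points, and lists the PEI and GRS among the instruments. Data Collection describes the survey differently: "The 550 patients in the PEP programme who are willing to take part in the telephone survey" are the only people it mentions contacting.

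**What is asked.** Appendix D prints one follow-up form, with no version for controls.
- PEI, English: "As a result of your participation in Shared-Care Programme"
- GRS, English: "How would you rate the change in your health condition after participating in the Shared Care Programme"
- PEI, Chinese: "參加了共同護理計劃後,您感到以下的情況有何改變"
- GRS, Chinese: "參加了共同護理計劃後, 您認為您的身體健康情況比之前是"

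The Chinese stems also ask about change after joining the Shared Care Programme. The introduction to the same form names the PEP. The Shared Care Programme appears nowhere else in the text at hand.

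**What is to be analysed.** Both scores are secondary outcomes. Data analysis item 2 puts patient-reported outcomes under a paired t-test over time. Item 3, the comparison with controls, names clinical and service-use outcomes only. Hypothesis 5 expects patients to report improvement after the programme and mentions no comparison group.

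**The concern.** Neither item has a baseline, so a comparison with similar patients outside the programme is the only route the protocol offers from these scores to a statement about the PEP's effect. That comparison requires both groups to answer the same question with the same meaning. The printed stems make this impossible, because they take as given something that is true of one group only.

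In addition, the form sends participants to a different programme's name, so even their answers are not clearly about the PEP. At stake is whether the enablement and global-change results can be interpreted at all, and whether a later report could present control answers as though they were comparable.

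**Working it through.** **1. The plan's own figure.** Sample size calculation: effect size 0.3, 80% power, independent t-test, two-sided 5% level (inferred from the 95% confidence interval).
- Per group n = 175, as stated; the exact t-test calculation gives 175.4, with power 0.799 at 175.
- Inflation for four losses of 25%: 175 / 0.75^4 = 553, against 550 stated.
- Remaining at the last follow-up: 550 × 0.75^4 = 174.

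The figure reproduces. It was derived for quality of life, which the wording problem does not touch, so it neither causes nor cures the defect.

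**2. Who answers, side by side.**
- Abstract and Subjects: both groups answer the PEI and GRS.
- Data Collection: only PEP patients are described as contacted.
- Hypothesis 5 and Data analysis item 3: no control comparison on these items.

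These places do not agree on whether non-participants are asked.

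**3. What a non-participant can say if asked.**
- PEI: six items scored 0, 1 or 2, so the range is 0 to 6 × 2 = 12. *Same* and *less* both score 0. The other truthful choice is *not applicable*, which carries no score. The control score is therefore missing or at the floor.
- GRS: seven points from -3 to +3, with no not-applicable column. The respondent must choose *same* or rate a change from an event that did not happen.

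**4. Form against Methods.** Data Collection defines the GRS as perceived change in overall health over six months, with no condition of participation. The printed GRS asks for change after participating and states no period. The form therefore does not measure what Methods defines.

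**5. Can the paired test replace the controls?** A paired test from baseline needs follow-up minus baseline for each patient. Data Collection introduces the PEI and GRS only at the follow-up interviews, the Appendix D baseline form omits them, and the footnote in Appendix C limits them to 6 months. The Subjects sentence, read alone, could suggest that they are also asked at the first interview, but the baseline form does not bear that out. With no baseline value there is no such difference to test.

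**6. Reach.** The SF-12 items and the private-service questions contain no participation premise. None of the primary outcomes uses the PEI or GRS.

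**The case against.** The strongest reply is that no listed test compares PEI or GRS between groups. Data analysis item 3 leaves patient-reported outcomes out, hypothesis 5 concerns patients in the programme, and Data Collection speaks of PEP patients only. Both instruments are change ratings and can be read in participants alone. On that reading, the only error is a wrong programme name, on a call already introduced as concerning the PEP.

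Much of this stands. A reader might infer that a pre-specified between-group test is invalid; the document does not support that, because no such test is written for these two scores. What remains is that the Abstract gives evaluation of enablement and global change as a reason for recruiting non-participants, and Subjects puts the items to every consenting subject. Followed as written, the plan collects control answers that mean nothing. A participant-only reading is workable, but then the Abstract and Subjects must say so, and the paired test must be replaced for these scores.

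A reader might also infer a calculable false benefit. If every control is set to 0 and participants average +0.3 on the GRS (SD 1), then with 412 per group (550 × 0.75, rounded down) z = 0.3 / (1/√412) = 6.1. That mean and SD are invented, and fixing all controls at 0 assumes the conclusion. On the PEI the equally plausible result is missing data. The document gives no basis for a size of bias.

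**Conclusion.** The point holds as a conflict between the design text and the questionnaire, confined to two secondary outcomes. If the Abstract and Subjects are followed, every surveyed non-participant (550, or 550 per cluster as those sections read) is asked two questions whose premise does not apply. The answers are then missing, at the floor or arbitrary. Participants are asked about a programme other than the one under evaluation. The listed paired test offers no substitute.

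Two assumptions are made. First, non-participants have not joined a Shared Care Programme either; the protocol does not say, and any who had would be rating something other than the PEP. Second, the printed form is the one used for both groups, since no other is shown.

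It would be wrong to infer that patient-reported outcomes fail as a whole. The protocol lists four (SF-12v2, PEI, GRS and disease knowledge), and the quality-of-life comparison that sets the sample size is sound on this point. Nor can one say from this document whether the printed PEI stem departs from the validated one, because the validated wording is not given.

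**What to change.** **Preferred.** In both languages, replace the two stems with one neutral stem that names no programme and uses a fixed six-month reference period, as Data Collection already gives for the GRS. Read it identically to both groups. Reword the introductions to the baseline and follow-up interviews so that they are true for someone outside the PEP; the baseline one now tells each respondent that the programme's effect on them is being evaluated. State in Data Collection that both groups are interviewed.

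**Alternative.** Give the PEI and GRS to PEP participants only, name the PEP in the stems, report both descriptively, and remove enablement and global change from the between-group aim in the Abstract and Subjects.

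**Cost.** Either route means rewording two stems and a few sentences, which is cheap before follow-up interviewing starts. Answers collected with the present wording cannot be repaired by analysis. The preferred route alters the PEI's existing stem, so its validation may not carry over fully. A six-month period also means that the 36- and 60-month interviews would capture recent change and not change since enrolment. The alternative avoids a new neutral stem but gives up any control-based statement on these outcomes.

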**MUCH NOT**

**BETTER BETTER SAME LESS APPLICABLE**

**2 1 0 0**

able to cope with life

able to understand your illness

able to cope with your illness

able to keep yourself healthy

**MUCH NOT**

**MORE MORE SAME LESS APPLICABLE**

**2 1 0 0**

confident about your health

able to help yourself

**Global Rating on Change Scale**

How would you rate the change in your health condition after participating in the Shared Care Programme?

| **MUCH BETTER** | **BETTER** | **A LITTLE BETTER** | **SAME** | **A LITTLE WORSE** | **WORSE** | **MUCH**  **WORSE** |
| --- | --- | --- | --- | --- | --- | --- |
| +3 | +2 | +1 | 0 | -1 | -2 | -3 |

-------------------------------------------------end-----------------------------------------------

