## Hypotheses

The following hypotheses will be tested:

1. The criteria on structure and process should be achieved by all participating clinics and NGO;
2. More patients with DM will achieve the target HbA1c after 12, 24, 36 and 48 months in the PEP programme;
3. More patients with HT or DM will achieve the target blood pressure levels after 12, 24, 36 and 48 months in the PEP programme;
4. In longer terms, HT/ DM patients will have reduced cardiovascular risks and fewer complications;
5. Patients should report an improvement in quality of life (QOL), enablement and overall health condition after the PEP programme;
6. Patients who take part in PEP programme should not have any increase in service utilization rates.

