  2. The Patient Enablement Instrument (PEI) is a measure of patient’s enablement in coping with the illness and life (Howie, Heaney et al. 1998). It has 6 items each rated on a 3-point (0, 1, and 2) scale. The summation of the item scores gives the PEI score with a higher score indicating better enablement. The PEI has been translated into Chinese and shown to be valid and reliable in the general Chinese population (Lam, Yuen et al. 2010).
  3. The Global Rating Scale (GRS) is adapted from those used in studies by Jaeschke and Osoba et al (Jaeschke, Singer et al. 1989; Osoba, Rodrigues et al. 1998). It assesses the subject’s subject global perception of any change in the overall health condition on a 7-point scale (-3, -2, -1, 0, 1, 2, and 3) over the six months.

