**Secondary**

- Clinical outcomes including LDL and BMI.
- Cardiovascular complications.
- Renal complications.
- Patient reported outcomes (PRO) measured by the change in SF-12v2 scores, the PEI and GRS scores at 6, 12, 36 and 60 months, and change in patient’s knowledge on disease at 12 months.
- GOPC consultation, SOPC, A&E and hospital attendance rates in the past 12 months; the audit cycle will be repeated annually over a period of 5 years.

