## Data analysis

1. Descriptive statistics on standard of care will be calculated, including percentage of centers meeting each structure criterion, percentage of subjects enrolled, dropped out, completion of the programme, receiving criterion process, investigations and referral per protocol, and percentage of subjects achieving the criterion outcome.
2. The change in clinical, service, and patient reported outcomes after the PEP programme at baseline, 6, 12, 36 and 60 months will be compared by paired sample t-test. The audit cycle will be repeated annually over a period of 5 years.
3. Independent sample t-test or Chi square test as appropriate will be used to compare the clinical and service utilization outcomes between PEP patients and controls.
4. Independent sample t-test or Chi square test as appropriate will be used to compare the clinical and service utilization outcomes between results in achieved in different audit cycles.
5. Cost effectiveness analysis (CEA) by mathematical modeling will be carried out by using cost and clinical outcome data provided by the HA, as well as quality-of-life and private service utilization cost data collected by the telephone surveys.

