**Patients require special treatment:**

| **Data Required** | **Number of  patients** | **Time (in days) from problem recognition** |
| --- | --- | --- |
|
| Identified to have problem being given treatments per protocol |  |  |
| Referred for additional service |  |  |
| Refused additional service |  |  |

| **Time (Month)** | **Data required** |
| --- | --- |
| 0, 12, 24, 36 and 48 | **Clinical data** |
| HbA1c |
| Systolic BP |
| Diastolic BP |
| BMI |
| LDL-C |
| **Service utilization** (in the past 12 months) |
| Number of hospitalization |
| Number of A&E attendance |
| Number of GOPC consultation |
| Number of SOPC consultation |
| 0 and 6 months | **Patient reported** |
| Disease knowledge score |
| QoL score |
| PEI* |
| GRS* |

BP = Blood Pressure; BMI = Body Mass Index; LDL-C = Low density Lipoprotein Cholesterol; GOPC = General Outpatient Clinic; SOPC = Specialist Outpatient Clinic; KAP = Knowledge, Attitude and Practice.

*Measured at 6 months only.

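### The Global Rating Scale is already a rating of change and has no baseline, so the paired t-test that the protocol assigns to patient reported outcomes cannot show whether overall health improved

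*Protocol*

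**What the plan says.** Hypothesis 5 of the protocol reads "Patients should report an improvement in quality of life (QOL), enablement and overall health condition after the PEP programme". The GRS is one of the instruments that serve it. The Data Collection section defines it as the patient's "global perception of any change in the overall health condition on a 7-point scale", with six months as the period rated. The follow-up survey in Appendix D words the item as "How would you rate the change in your health condition after participating in the Shared Care Programme", with answers from +3 (much better) through 0 (same) to -3 (much worse). That form names the Shared Care Programme and not the PEP, which is a separate matter of wording; here it is taken to mean the programme under evaluation.

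On timing, the Data Collection section gives at entry only the "Short Form-12 version 2 (SF-12v2) Health Survey within one month from enrolment". From 6 months on, patients are "to repeat the SF-12v2 together with the Patient Enablement Instrument (PEI), Global Rating Scale (GRS) of change in health condition". The secondary outcomes list "the PEI and GRS scores at 6, 12, 36 and 60 months". Appendix C marks the GRS and PEI with the note "Measured at 6 months only". The baseline questionnaire in Appendix D contains neither instrument.

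On analysis, item 2 of the Data analysis section states that the change in "patient reported outcomes after the PEP programme at baseline, 6, 12, 36 and 60 months will be compared by paired sample t-test". It makes no exception for the GRS or PEI. Items 3 and 4 of that section, which give the independent t-test or chi-square test, are limited to clinical and service utilization outcomes.

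**The concern.** A paired t-test of change suits a measure of state taken before and after, such as the SF-12v2. The GRS is not a measure of state: the patient has already made the comparison, and the answer is the change. Whether patients feel better is read from how far the mean lies from 0. Subtracting one GRS score from another gives the difference between two ratings of change, which is a different question from the one in hypothesis 5.

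If item 2 is applied to the GRS as written, a group that reports the same improvement at every visit gives a null result, and so does a group that reports the same deterioration. A group that feels better throughout, but by less at the later visit, gives a significant fall.

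**Working it through.** **Which pairs exist.**

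| Source for GRS timing | GRS scores available | Pairs for item 2 |
|---|---|---|
| Appendix C | 6 months | none |
| Data Collection; secondary outcomes | 6, 12, 36, 60 months | follow-up against follow-up only |
| Subjects section, read literally | also within four weeks of recruitment | a pair with entry, but the baseline form has no GRS item |

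On no reading supported by the questionnaires is there a baseline GRS. A paired test could answer the question only if every patient's baseline were set to 0. That is a one-sample test against 0, which the protocol does not state.

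**The protocol's own sample size, for the numbers available.** Per group, n = 2(1.96 + 0.84)²/0.3² = 15.68/0.09 = 174.2, rounded up to 175, as stated. With 25% loss at each of four follow-ups, 175/0.75⁴ = 553, against the stated 550. These figures reproduce. They concern quality of life, and the present point does not depend on them. They give 550 × 0.75² = 309 per group at month 12 (second follow-up) and 550 × 0.75⁴ = 174 at month 60.

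**Analytic illustration at n = 309, two-sided 5%.** The means, SDs and correlation are assumptions.

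- Constant mean of +0.5. The expected difference between visits is 0, so the paired test rejects only at its 5% error rate. For the one-sample test against 0 with SD 1.2, the noncentrality is 0.5 × √309/1.2 = 7.3 and power exceeds 0.99. With SD 2.0 it is 0.5 × √309/2.0 = 4.4 and power is 0.992.
- Mean falling from +1.0 to +0.75, SD 1.2, correlation 0.5. The SD of the difference is √(2 × 1.2² × (1 - 0.5)) = 1.2, the noncentrality is 0.25 × √309/1.2 = 3.7, and the paired test declares a fall with power of about 0.955, although both means are on the better side of 0.

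**Simulation on the actual scale.** Scores were rounded and clipped to -3 to +3, with SD 1.2, correlation 0.5, n = 175 and 2000 runs. Means are those set before rounding.

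| Mean at earlier, later visit | Paired: significant rise | Paired: significant fall | Later visit significantly above 0 |
|---|---|---|---|
| 0, 0 | 2.5% | 3.4% | 2.3% |
| +0.5, +0.5 | 2.9% | 2.7% | 99.9% |
| +1, +1 | 3.0% | 2.3% | 100% |
| -1, -1 | 2.5% | 2.3% | 0% |
| +1.5, +1.0 | 0% | 99.9% | 100% |
| -1.5, -1.0 | 100% | 0% | 0% |

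The pattern at n = 309 is the same. The paired test does not separate the improved group (+1, +1) from the worsened group (-1, -1); the test against 0 does.

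**The PEI.** Its items also ask about change as a result of participation, and it too is absent from the baseline form, so it has no baseline pair either. Its scoring gives 0 both to the same and to less, so its score cannot go below 0, and a test against 0 would not serve it as it serves the GRS.

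**The case against.** Item 2 never names the GRS. The secondary outcomes can be read as separating change in SF-12v2 scores from GRS and PEI scores at a visit, in which case item 2 was meant only for measures with a baseline. No sentence sets out a 12 against 6 month GRS comparison, and a statistical analysis plan may give an instrument-specific test. This stands in part. The GRS is covered by class and not by name, and nobody can say from this document that a test against 0 will never be done. But the secondary outcomes place the GRS among the patient reported outcomes, and item 2 fixes a test for that class, baseline included, without exception. The point is about a stated method that does not fit, not about missing detail.

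A reader might infer more than the documents support:

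- That hypothesis 5 rests on the GRS alone for overall health. It does not. The SF-12v2 has a general health domain, and its first item asks about general health at baseline and at follow-up, so a paired test is suitable there.
- That the paired t-test is the only test planned for any patient reported outcome. The sample size section bases the quality-of-life evaluation on an independent t-test between participants and non-participants.
- That the report would state the opposite of what patients said. That requires ignoring the visit means: +1.0 and +0.75 show improvement on their face. Under Appendix C's timing there is no second score, so neither the null result nor the false fall could arise.
- That a fall between visits always leaves patients above where they started. This depends on the recall period. Data Collection has patients rate the six months; Appendix D has them rate change since taking part. With a six-month recall, successive ratings cover different intervals, and a fall from +1.0 to +0.75 means further but smaller gain. The paired test still does not show whether health improved.

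**Conclusion.** The point holds in a limited form. As written, the paired t-test in item 2 either has no GRS pair to work on or compares one change rating with another, and in neither case can it show improvement in overall health. This follows from the wording and schedule of the instrument and needs no numerical assumption. The power and simulation figures are illustrations under an assumed mean, SD (1.2, with 2.0 as a check) and correlation (0.5).

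The effect is confined to the GRS, with a similar problem for the PEI, inside one secondary outcome. The SF-12v2, the primary outcomes and the sample size are untouched. The protocol also disagrees with itself on when the GRS is asked and over what period, and the result of any test depends on settling that.

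**What to change.** In the Data analysis section:

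1. Take the GRS out of item 2. Among PEP participants, test the rating against 0 at each follow-up at which it is taken (one-sample t or signed-rank test), and report the proportions better (+1 or more), same (0) and worse (-1 or less).
2. Take the PEI out of the paired test as well and report its score at each follow-up.
3. Keep the paired test for the SF-12v2.
4. Compare the GRS between participants and non-participants only if non-participants are asked a version that does not refer to participation. The Subjects section gives the survey to both groups, but the present item asks about change after taking part, which non-participants cannot meaningfully answer.

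Elsewhere, reconcile the GRS timing across Subjects, Data Collection, the secondary outcomes and Appendix C, and the recall period between Data Collection and Appendix D.

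The analysis changes take a sentence or two and use data already planned, with no added visits or patients. Only a between-group GRS comparison would need a reworded question.
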